## Abstract

Pain is an under-reported but prevalent symptom in Parkinson’s Disease (PD), impacting patients’ quality of life. Both pain and PD conditions cause cortical excitability reduction and non-invasive brain stimulation. Mental representation techniques are thought to be able to counteract it, also resulting effectively in chronic pain conditions. We aim to conduct two independent studies in order to evaluate the efficacy of transcranial direct current stimulation (tDCS) and mental representation protocol in the management of pain in PD patients during the ON state: (1) tDCS over the Primary Motor Cortex (M1); and (2) Action Observation (AO) and Motor Imagery (MI) training through a Brain-Computer Interface (BCI) using Virtual Reality (AO + MI-BCI). Both studies will include 32 subjects in a longitudinal prospective parallel randomized controlled trial design under different blinding conditions. The main outcomes will be score changes in King’s Parkinson’s Disease Pain Scale, Brief Pain Inventory, Temporal Summation, Conditioned Pain Modulation, and Pain Pressure Threshold. Assessment will be performed pre-intervention, post-intervention, and 15 days post-intervention, in both ON and OFF states.

## 1. Introduction

Parkinson’s Disease (PD) affects between 4.1 and 4.6 million people in the world [1]. The diagnosis of PD is currently clinical and based on its motor manifestations (bradykinesia, rest tremor and rigidity). However, non-motor symptoms such as pain, fatigue, and neuropsychiatric manifestations are present in more than 70% of subjects [2].

Pain affects about 85% of patients [3] but is paradoxically under-reported [4] and consequently under-treated in PD patients with a great impact in their quality of life [5]. Levodopa, which is the election treatment in PD, has shown controversial results regarding pain sensitivity [6,7] and has been shown to be ineffective for enhancing the endogenous pain modulation system [8]. Furthermore, there is a lack of management protocols and nonpharmacologic treatments for pain in PD [9].

Several syndromes are hypothesized to be involved in PD pain generation [10]. Generally, PD patients suffer from alterations in peripheral transmission, sensitive-discriminative processing, pain perception and pain interpretation in multiple levels, due to neurodegenerative changes in dopaminergic pathways, and non-dopaminergic pain-related structures [11]. Therefore, central mechanisms are proposed to be crucial for the development and establishment of pain in PD patients [12].

Regarding to pain processing features, PD patients have reduced pain thresholds [7], an augmented Temporal Summation (TS) after repetitive nociceptive stimulus [13] and the impairment of their Conditioned Pain Modulation (CPM) is correlated with a greater severity and premature onset of the disease [8].

Cortical excitability reduction is common in patients with pain [14]. Therefore, diverse therapies are being developed to counteract this cortical excitability reduction and consequently obtain effective pain relief [15,16]. In consonance with these findings, in PD condition, especially when levodopa is not acting (OFF state), there is also evidence of a decrease in cortical excitability [17]. However, PD patients have also shown to present an excessive corticospinal output at rest, associated with reduced intracortical inhibition, and impairments of intracortical facilitatory inputs during movement preparation and execution. Consequently, PD patients reveal motor cortex disfunction, which could be a valid target for therapeutic neuromodulation [18]. To the best of our knowledge, there are no studies targeting cortical excitability to treat pain in PD.

Thus, the present study protocol proposes two innovative non-pharmacologic approaches for the treatment of pain in PD patients, which incorporate current knowledge on physiological mechanisms and the clinical results of neuromodulation therapies used in other pain populations. Both protocols are based on neuromodulation, one of them through non-invasive brain stimulation and the other through mental representation techniques. Both protocols will be compared with respective placebo control groups, in order to evaluate their therapeutic effect, eliminating systematic errors such as expectations-related influences in the effect of the therapy as well as its potential adverse effects.

The non-invasive brain stimulation therapy will be transcranial direct current stimulation (tDCS) over the Primary Motor Cortex (M1). A tDCS over M1 is capable of increasing corticospinal excitability in both M1 and other pain processing-related areas such as thalamus, Dorsolateral Prefrontal Cortex (DLPFC), cingulate cortex and insula [15,16], also involved in PD pain processing [12]. These increments of cortical excitability have been correlated with pain relief in chronic pain such as fibromyalgia [19], osteoarthritis [20], migraine [21], and spinal cord injury [22]. It is also hypothesized that tDCS would be an effective strategy to treat central sensitivity-related pain [23], a process whose features are common with PD condition [3]. Moreover, specifically in PD, tDCS over M1 have shown to increase cortical excitability, augmenting the Motor Evoked Potential (MEP) amplitude by 78.5%, correlating with motor improvements [24]. The altered descending inhibitory systems in chronic pain could also be improved with high frequency repetitive transcranial magnetic stimulation, by increasing cortical excitability [25].

For the most part, the hypoalgesic effects generated by tDCS are due to the adjustment of its effect on the Primary Motor Cortex (M1). It is suggested that tDCS on M1 could reduce pain by increasing excitability, not only of the stimulated area, but also of other structures involved in pain processing, both sensory and emotional, such as the thalamus, dorsolateral prefrontal cortex (DLPFC), cingulate cortex, insula, and brain stem [15,16], thanks to cortical-subcortical connectivity [26].

Due to the coincidence between many of the most influential areas of pain in PD [12] and the areas excited by tDCS on M1, with these increases in excitability correlating with decreases in pain [15,16], there is a possible beneficial interaction between tDCS on M1 and pain in PD.

The mental representation techniques included in the protocol will be Action Observation (AO) and Motor Imagery (MI). In the same way, the combination of AO and MI has shown to synergically increase cortical excitability [27], influencing the activation of cortical areas such as M1 and DLPFC [28]. Specifically in PD, they also have demonstrated to produce corticomotor facilitation [29]. In addition, mental representation training can produce neurophysiological activity similar to actual exercise training [30], which have shown to decrease the intensity and severity of pain in PD patients [31].

There are no studies correlating effects of pain non-invasive neuromodulation with complete neuropsychological evaluation including computerized reaction time tasks and extensive neurophysiological measures such as direct cortical excitability evaluation using TMS and connectivity based in EEG entropy analysis. All these features have been described to be altered in PD and Pain.

The main aim of this study is to conduct two independent parallel randomized controlled trials based on both neuromodulation techniques targeting changes in 1. validated general and specific PD related pain scales 2. psychophysical measurements of pain modulation mechanisms and 3. wide neuropsychological and neurophysiological evaluation. Our main hypothesis is that both active neuromodulation techniques will be superior to their respective control placebo interventions. If this hypothesis is confirmed a further analysis of superiority will be proposed among both protocols.

## 2. Materials and Methods

The SPIRIT 2013 checklist has been used to assure the quality of the protocol [32].

### 2.1. Study Design and Participants

The participants will be recruited in PD outpatient’s clinic of the Beata María Ana Hospital of Madrid, Spain. The subjects included will be assessed by a neurologist expert in movement disorders. All patients will be idiopathic PD patients diagnosed according to the UK Parkinson’s Disease Society Brain Bank criteria who suffer from whatever PD-related pain, determined by The Parkinson’s Disease Pain Classification System (PDPCS) [33] and with a pain intensity of 3 out 10 points in the Visual Analogue Scale (VAS) while in ON state, that is, when levodopa is acting. The rest of specific inclusion criteria and the exclusion ones are listed in Table 1 and Table 2. During the protocol, changes in analgesic medication during in the previous week or PD treatment in the previous month will be forbidden and if necessary, will lead to exclusion of the patient. Informed consent for all included procedures (therapies and outcomes measurement), approved by the ethics committee, will be obtained from all subjects before their inclusion, and both studies will follow the principles outlined in the Declaration of Helsinki.

Sensitive data for all participants will be registered separately, anonymized, and guarded according to current data protection European laws. All data will be registered and double checked in a database designed specifically for the studies.

Recruitment in both protocols will be made so placebo and active groups will be matched by age and the recruitment will be stratified in groups of subjects younger than 60 years and older than 60, always ensuring that there is an equitable number of subjects in the two sections.

It is well known that there are gender differences in pain thresholds in healthy humans [34] and some evidence suggests that greater disease severity, female gender and higher doses of mediation are associated with greater pain intensity in PD [35]. For this reason, inclusion of at least one third of female subjects will be assured. Disease severity and total dopaminergic daily dose will be controlled in the final analysis of results.

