### 2.2. Intervention Protocols

In both studies, PD patients, independently of the group allocation, will undergo 10 sessions in two weeks (Monday to Friday). All sessions will be performed during ON state of patients and with their usual analgesic medication, to ensure their comfort.

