During interventions, all subjects will be seated in a relaxed position in spite of this technique have demonstrated to be safe and pleasant [41]. When “on demand” analgesic medication is part of the usual treatment of the patient, the daily doses used will be registered to follow the short-term efficacy of the protocol. Our protocol follows the security and replicability recommendations for the use of this technique [42]. Possible adverse effects [41] will be assessed after each session by the Comfort Rating Questionnaire (CRQ), a modified version of the unpublished questionnaire from the Göttingen study group [43,44], and its apparition could lead in the interruption of the intervention. Although no severe adverse effects are expected. Any adverse effect will be notified to a licensed medical doctor. Management of possible adverse effects will be individualized and according to the severity. In case of headache or scalp pain, an extra dose of analgesics will be prescribed if necessary and recorded for each patient, in case of skin local reactions such as reddening or itching local application of talcum will be suggested. In case of sleep changes, concentration problems, mood changes, or any other non-previously described adverse effects detected in the daily post treatment assessment will be managed individually and in case of persistence the medical doctor will make the decision to suspend the protocol for the patient and set a follow-up until the symptoms are resolved.

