### 2.3. Outcomes Measurement

The same outcomes will be included in both studies. All of them will be assessed by a trained physical therapist in all groups the previous week, the following week, and 15 days after the 10 intervention sessions. The procedure is presented in Figure 1.

Every outcome will be measured in the ON state of PD patients, 1 h after taking their dopaminergic medication, to ensure their comfort. Nevertheless, Kings Parkinson’s Disease Pain Scale (KPDPS), CPM and TS will be also measured in OFF state, 30 min before medication intake, to assess the effects of both neuromodulation therapies when dopaminergic medication is not acting.

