### 2.5. Data Analyses

The SPSS software package (version 25.00; SPSS inc., Chicago, IL, USA) will be used by a blinded statistician for statistical analysis of the data. Demographic and clinical variables will be presented as mean and standard deviation. A 95% confidence interval (CI) will be taken, considering statistically significant all those values that had a *p* < 0.05. Parametric statistical tests will be used for hypothesis testing (*n* > 30). To show differences in the main variables, an analysis of variance (ANOVA) 2 × 3 of repeated measurements will be carried out taking time and group as factors, being the groups active-tDCS (a-tDCS) vs. sham-tDCS (s-tDCS) in the tDCS-based study and AO+MI-BCI vs. AO-control AO+MI-based study, and the measurements times pre-treatment, post-treatment, and at 15 days post-treatment. If significant differences are found in any of the interactions, a post hoc analysis will be performed with Bonferroni correction. The effect sizes will be calculated by means of the d of Cohen, being classified as small (d between 0.20 and 0.49), medium (d between 0.50 and 0.79), or large (d greater than 0.80) following the method of Cohen.

For the rest of the psychological variables, a Pearson’s correlation with the physical variables will be carried out in order to find relationships between both. Low correlation will be taken as that with values between 0.2 and 0.39; the correlation will be considered moderate when the value goes from 0.40 to 0.79; and high when the value of the correlation is greater than 0.80.

For the analysis of neurophysiological variables rMT, MEP magnitudes will be determined by averaging peak-to peak amplitudes. The ratio of the rMT, MEP amplitude recorded at each post-intervention time-point relative to the baseline rMT will be calculated [(MEP amplitude at each stage–baseline MEP amplitude)/baseline MEP amplitude Å~100]. Statistical analyses will be performed on the calculated test-to baseline MEP ratios. For the CSP values the time will be measured manually in each trial and averaged and the ratio compared to baseline measurement will be also calculated.

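### The medication rule in section 2.1, most naturally read as an on-study rule, excludes randomised patients who need a regimen change, a reason tied to pain for analgesics and possibly for PD drugs

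*Protocol article*

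**What the plan says.** The rule is one sentence in section 2.1 (Study Design and Participants). It opens "During the protocol, changes in analgesic medication", and the full condition is "analgesic medication during in the previous week or PD treatment in the previous month will be forbidden and if necessary, will lead to exclusion". It comes just after the pointer to the eligibility tables: "The rest of specific inclusion criteria and the exclusion ones are listed in Table 1 and Table 2". Neither table contains a medication-stability criterion.

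Other provisions limit the rule to changes of regimen:
- Section 2.2 permits existing analgesics: "All sessions will be performed during ON state of patients and with their usual analgesic medication".
- Sections 2.2.1 and 2.2.2 permit on-demand doses that belong to the usual treatment. They are recorded as a guide to short-term efficacy.
- Section 2.2.1 permits an extra analgesic dose for headache or scalp pain in the tDCS study.

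Outcomes are assessed "the previous week, the following week, and 15 days after the 10 intervention sessions" (section 2.3). The sample size is based on the King's Parkinson's Disease Pain Scale as primary outcome, with 16 patients per arm in each study (section 2.4). The main analysis is a 2 × 3 ANOVA "of repeated measurements will be carried out taking time and group as factors" (section 2.5). The only follow-up described after stopping concerns adverse effects, where the doctor may "suspend the protocol for the patient and set a follow-up until the symptoms are resolved" (section 2.2.1; similarly 2.2.2).

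**The concern.** A need for a new analgesic regimen during a pain trial is in large part a report of how the pain is going. The article itself treats on-demand analgesic use as a signal of efficacy. Excluding randomised patients for that need selects on something close to the outcome, after treatment has had a chance to act on it. The link is weaker for PD treatment, which may be changed for motor reasons, but a relation to pain is possible.

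If excluded patients also leave the assessments, the two arms are no longer the groups that were randomised. The retained contrast then depends on who was removed from each arm as well as on the treatment. A repeated-measures ANOVA in its standard form uses only patients with all three visits, so it would not bring them back. A later analysis plan can define analysis sets, but it cannot recover visits that were never made.

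**Working it through.** **Step 1: entry rule or on-study rule?**

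For on-study: the sentence opens by referring to the protocol period; a change can be forbidden only in advance; and a change that becomes necessary and then leads to exclusion describes someone already in the study.

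For entry: the one-week and one-month windows look backwards, as eligibility windows do, and the sentence sits beside the eligibility text.

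The visit calendar does not decide it. Take Monday of week 1 as day 1. The tenth session is then Friday of week 2, day 12, and the last visit is day 12 + 15 = day 27.
- PD treatment: one month back from day 27 reaches before day 1, so the window covers every session.
- Analgesics: one week back from day 27 is day 20, after the last session. One week back from the post-treatment pain visit (the Thursday of the following week in Figure 1, day 18) is day 11. Anchored at these visits, the window would miss a change on days 1 to 10.

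The calendar therefore fits an on-study reading for the PD window only. The on-study reading rests on the sentence's wording.

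**Step 2: what could exclusion do to the estimate?**

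The article gives no exclusion rate, so every input here is assumed. Let improvement be N(0, 1) in control and N(d, 1) in active. A patient is excluded when a latent state, with the same arm shift and correlation r with the outcome, falls below −c. The threshold is the same in both arms and is set by the control exclusion rate: c = −z(rate).

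Mean among retained patients in an arm with mean μ:

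μ + r · φ(a) / (1 − Φ(a)), with a = −c − μ.

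Worked case: d = 0.5, 10% of controls excluded, r = 1, so c = 1.282.
- Control: a = −1.282; 0.1755 / 0.90 = 0.195.
- Active: a = −1.782; Φ(a) = 0.037, so 3.7% are excluded; 0.0815 / 0.963 = 0.085; retained mean 0.585.
- Retained difference: 0.585 − 0.195 = 0.390 SD.

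| Controls excluded | c | Active excluded | Patients out of 16 (control / active) | Difference, r = 1 | Difference, r = 0.5 |
|---|---|---|---|---|---|
| 5% | 1.645 | 1.6% | 0.8 / 0.3 | 0.432 | 0.466 |
| 10% | 1.282 | 3.7% | 1.6 / 0.6 | 0.390 | 0.445 |
| 15% | 1.036 | 6.2% | 2.4 / 1.0 | 0.356 | 0.428 |

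A simulation with 2 million patients per arm at the 10% rate gave 0.390 and 0.445. With d = 0 the two arms lose the same share from the same distribution, and the difference is 0 at every rate and every r.

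Across the table the loss runs from 0.5 − 0.466 = 0.03 SD to 0.5 − 0.356 = 0.14 SD. For scale, the standard error of a two-arm difference with 16 per arm and SD 1 is √(2/16) = 0.35 SD.

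**The case against.** The strongest reply is that this is an awkwardly written stability criterion. The windows look back, the neighbouring text is about eligibility, and elsewhere the article describes stopping on study as interrupting the intervention or suspending the protocol, not as exclusion. The absence of the criterion from Tables 1 and 2 proves little, since those tables hold only the remaining criteria; the diagnosis and pain-intensity requirements also appear only in the text. This stands in part: the entry reading is available. It does not remove the point, because the sentence as written covers patients already in the study, and the same edit resolves either reading.

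Second, exclusion is not defined. It may mean leaving treatment, assessment or analysis, and a fuller protocol or an analysis plan may say which. This also stands, so the bias is conditional. A reader might infer that excluded patients are certainly dropped from follow-up and analysis; the article does not say so. It only describes no route that keeps them in.

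Third, exclusions may be few, because usual, on-demand and some extra doses are allowed over about four weeks. The top scenario uses up in the control arm the same 15% that section 2.4.1 allows for all losses, and r = 1 is extreme. The modelled attenuation is also small beside the sampling error. All of this is fair, and it limits the weight of the point.

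Fourth, keeping patients who change regimen also dilutes the contrast, and holding co-medication fixed is a recognised choice in a short trial. That stands as a cost. It does not justify removing the patients who needed the change.

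**Conclusion.** The point holds in conditional form and is worth fixing, with medium confidence. The rule is stated in the article, so this is not a complaint about an omission. Read as an on-study rule, it excludes randomised patients for a reason closely tied to the pain outcome (analgesics) or possibly related to it (PD treatment). If exclusion ends outcome assessment, the estimate can be biased.

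The size cannot be derived from the documents. Under the assumed model, a true 0.5 SD effect shrinks to between 0.36 and 0.47 SD when 5% to 15% of controls are excluded.

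Three stronger readings are tempting and unsupported:
- That the rule manufactures a false positive. With a common threshold there is no bias under the null, and a true effect is attenuated. Other exclusion patterns could shift the estimate the other way, but nothing in the article points to one.
- That any analgesic use leads to exclusion. Usual and on-demand doses, and the extra dose in the tDCS study, are permitted.
- That a PD-drug change is as clearly linked to pain as an analgesic change. No section says so, and the introduction describes levodopa's effect on pain sensitivity as controversial.

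**What to change.** Split the sentence in two.

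1. **Entry criterion:** no change of analgesic regimen in the week before baseline and no change of PD treatment in the month before baseline.
2. **After randomisation:** regimen changes are discouraged but do not lead to exclusion. Every patient stays in the scheduled assessments and in the analysis of the assigned arm. The drug, date and reason of each change are recorded, and changes are reported by arm.

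The cost is a wording change and a short medication-change record. Part of the data is needed anyway, since section 2.1 says that "total dopaminergic daily dose will be controlled in the final analysis of results".

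The downside is that the estimate then includes the effect of any medication changes, with some dilution of the contrast. A sensitivity analysis that treats values after a regimen change as missing in a mixed model would show how much this matters.

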#### 2.1.1. tDCS-Based Study

This study will be a triple-blinded experimental longitudinal prospective randomized controlled trial with a parallel design. The randomization will be realized through the GraphPad software (GraphPad Software, San Diego, C.A., U.S.A.), by an independent investigator. All the participants who fulfill the inclusion criteria and have none of the exclusion one will be randomly allocated in two groups: active-tDCS (a-tDCS) or sham-tDCS (s-tDCS). Allocation concealment will be ensured by the inclusion of the assigned group in closed opaque envelopes that will be opened at the time of the intervention. Triple-blind criteria will be achieved by identic collocation of the electrodes in both groups and by activating the “double-blind” option in the Starstim tCS^®^ Software (Neuroelectrics Inc, Barcelona, Spain) that allows the protocol to be concealed by writing a neutral number. The investigator in charge of concealing allocation will also conceal the protocols with the neutral number and the therapist will read it in the envelope, ignoring which number coincides with each intervention. At the end of the full treatment, patients will be asked about which stimulation condition they think they received and how confident they are in their guess. After each session a tDCS adverse effects questionnaire will be applied, the patient will be asked about any symptoms that they have experienced during the session in order to be able to identify possible adverse effects not described. In addition, their comfort will be assessed using a specific comfort questionnaire specified in the protocol section. These questionnaires will be necessary to obtain quantitative information on tDCS tolerability and blinding maintenance, which is scarce in PD patients [36]. Patients recruited will not meet in waiting rooms to avoid them to comment on their experience during the protocol. The statistician will be also blinded through the mentioned neutral numbers. Unblinding will be permissible in any event where it could pose a risk for the patient’s health. The Institutional Research Committee and Institutional Ethics Committee of Hospital Universitario 12 de Octubre approved this study with code 20-515 on December 2020 and the trial was registered in www.clinicaltrials.gov number NCT04651699.

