### 2.4. Sample Size Calculation

#### 2.4.1. tDCS-Based Study

The simple size for the tDCS-based study was calculated using G*Power software (version 2.1, Heinrich-Heine-Universität Düsseldorf, Düsseldorf, Germany), taking into consideration the design of two intervention groups and three assessment times. The primary outcome was chosen to be King’s Parkinson’s Disease Pain Scale with an estimated effect size of F = 0.25. An α level of 0.05 and a power of 90% was assumed, with a total sample of 28 subjects estimated. Considering a 15% follow-up loss, we estimated a minimal sample size of 32 patients, with a minimal recruitment of 16 required for each of the intervention groups.

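### The plan promises age-matched arms but assigns the matching and the age strata to recruitment, which cannot balance age between arms under concealed random allocation

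*Protocol article*

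**What the plan says.** Section 2.1 (Study Design and Participants) sets a rule for both trials: "Recruitment in both protocols will be made so placebo and active groups will be matched by age". The same sentence goes on: "the recruitment will be stratified in groups of subjects younger than 60 years and older than 60", and ends "always ensuring that there is an equitable number of subjects in the two sections". The article does not say whether the two sections are the age groups or the treatment arms. A patient aged exactly 60 belongs to neither stratum.

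Section 2.1.1 describes allocation in the tDCS trial: "The randomization will be realized through the GraphPad software (GraphPad Software, San Diego, C.A., U.S.A.), by an independent investigator". Concealment rests on placing "the assigned group in closed opaque envelopes that will be opened at the time of the intervention". Section 2.1.2 gives the AO+MI trial the same software and envelopes but does not say who generates the list. Neither section links the list to age.

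Section 2.4.1 plans 32 patients, "with a minimal recruitment of 16 required for each of the intervention groups", and section 2.4.2 adopts the same total. Section 2.1 names disease severity and total dopaminergic dose as the variables to be controlled in the analysis. The main model in section 2.5 is a 2 × 3 repeated-measures ANOVA with time and group as its factors. Age appears in neither place.

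**The concern.** The stated aim is that the two arms be alike in age, and the stated means is recruitment. These do not fit together. Recruitment ends before the envelope is opened, so whoever selects patients does not know which arm the next one will enter. Recruiters can set quotas for younger and older patients in the sample, but they cannot decide how each age group divides between active and control. Only the allocation step can do that, and the allocation sections do not mention age.

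Two things are at stake. The first is that the arms may differ in age by chance, in trials of only 32 patients each, although the plan tells readers that they will be matched. The second is conditional: staff who take the instruction literally might try to achieve the match through whom they enrol and when, which concealment is there to prevent.

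**Working it through.** **What each step can control**

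| Step | What the article assigns to it | What it can fix |
|---|---|---|
| Recruitment (2.1) | Age matching of arms; strata under and over 60 | Age mix of the whole sample |
| Allocation (2.1.1, 2.1.2) | Random, sealed until the intervention; age not mentioned | Age mix within each arm |
| Analysis (2.1, 2.5) | Time and group; severity and dose to be controlled | Adjustment for named covariates; age not named |

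The article gives no figure for age balance, so there is none to reproduce. The check is how far apart the arms could be if quotas are met but the list takes no account of age.

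**Inputs**

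- From section 2.4.1: 32 patients, 16 per arm.
- Assumption: 16 patients under 60 and 16 aged 60 or over. This reads the equal numbers in section 2.1 as referring to the age groups.
- Assumption: a list fixed at 16:16 and not stratified by age.

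**Formula.** Let X be the number of under-60 patients in the active arm. Then X is hypergeometric:

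P(X = x) = C(16, x) × C(16, 16 − x) / C(32, 16) = C(16, x)² / 601,080,390

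**Results**

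- Exact balance, 8:8: 12,870² / 601,080,390 = 0.276.
- 10:6 or worse in either direction: 2 × (8,008² + 4,368² + 1,820² + 560² + 120² + 16² + 1) / 601,080,390 = 2 × 86,848,145 / 601,080,390 = 0.289.
- 11:5 or worse: the same sum without 8,008², 2 × 22,720,081 / 601,080,390 = 0.076.
- 12:4 or worse: 0.012.

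A 10:6 split means that 10/16 = 62.5% of one arm and 6/16 = 37.5% of the other are under 60, a gap of 25 percentage points.

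**Sensitivity**

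- With 28 evaluable patients (14 per arm, 14 per age group), 9:5 or worse has probability 0.257.
- With simple randomisation instead of a fixed 16:16 list, a gap of at least 25 points in the share under 60 has probability 0.216.

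So for list types that take no account of age, the chance of a gap of about this size is between one in five and three in ten.

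**After the change.** With 16 patients per age group and permuted blocks that complete, each group divides 8:8 and the difference is 0 by design. If the last block in a stratum is incomplete, the difference in that stratum is at most half the block size, for example 2 patients with blocks of 4.

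**The case against.** The strongest reply is that the sentence should be read whole. It joins balanced arms, age strata and equal numbers, and may be a loose account of age-stratified randomisation. Age balance and sealed envelopes are compatible when someone outside recruitment holds stratified lists, and section 2.1.1 names an independent investigator. A journal article may also leave list construction to the full protocol. This stands as far as it goes: the intention may be sound, and missing block sizes are not a finding. But the article places both the matching and the strata at recruitment. If stratified randomisation was meant, the sentence describes the wrong step and needs the same correction.

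A reader might infer that the matching rule breaches concealment and makes selection bias likely. The documents do not support that. Opaque envelopes opened at the intervention keep the next assignment from recruiters, and no text tells staff to look ahead or to steer. Bias would need staff to go around the envelopes to achieve the match.

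A reader might also infer that chance imbalance invalidates the comparison. It does not: type I error is preserved over repeated randomisations when allocation is random and concealed. Nor does the article name age as a driver of pain; it cites disease severity, female sex and medication dose. The group-by-time test also compares change, so a constant effect of age on pain level cancels and only an effect of age on change would matter. These points limit the harm. They do not make the stated promise true.

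**Conclusion.** The point holds in a limited form. Section 2.1 promises arms matched by age through a step that, under the concealed random allocation of sections 2.1.1 and 2.1.2, cannot match them. If the lists take no account of age, a 10:6 split or worse has probability about 29% and an 11:5 split or worse about 8%, assuming 16 patients per age group and a fixed 16:16 list. The article does not state the list type; if the lists are already stratified by age, these figures do not apply and only the wording is at fault.

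The main consequence is chance age imbalance that the stated ANOVA does not adjust for. Selection bias is a secondary risk, present only if staff try to match by steering enrolment. The validity of the randomised comparison is not in question. The gap at age exactly 60 is a small wording slip to close at the same time. The correction is worth making because it delivers the plan's own aim in both trials at almost no cost.

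**What to change.** Replace the statement that recruitment will match the arms by age with one that randomisation in each trial is stratified by age (<60, ≥60), in permuted blocks whose sizes are concealed from recruiting staff. State for both trials that the lists are generated and held by an investigator independent of recruitment; section 2.1.2 does not say this for the AO+MI trial. If quotas for younger and older patients are still wanted, describe them separately as a rule on the composition of the sample.

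Include the age stratum in the outcome model, and let it act on change over time as well as on level, since the treatment test is the group-by-time interaction.

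The cost is one extra list per trial and one model term. With 32 patients and three times, the error degrees of freedom for the interaction fall from (32 − 2) × 2 = 60 to (32 − 3) × 2 = 58. The sample size and patient procedures do not change. Balance is only approximate if blocks are left incomplete, so block sizes should be small relative to about 16 patients per stratum.
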